**Fig. 1 Fig1:**
[figure not shown]
Study flow chart of the MPP Narrow QRS trial. Data will be collected from enrollment to 24-month follow-up

**Table 2 Tab2:** List of all investigational-specific activities/procedures

	Time point	Enrollment	Implant	Pre-discharge	6-12-24 month follow-up	Implant	6-12-24 month follow-up
	Study activity	ALL patients		MPP group		Standard ICD group	
Enrollment	Low-dose dobutamine stress echocardiography	X					
	Informed consent process	X					
	Verification of inclusion/exclusion criteria	X					
	Demographics and medical history	X					
	Randomization	X					
Intervention:	MPP device implant		X				
	Standard ICD implant					X	
Assessment	Fluoro images and/or cine of venogram and final lead position, two projections		X			X	
	Capture thresholds and signal amplitude measurements on RA and RV leads		X	X	X	X	X
	Capture thresholds and phrenic nerve stimulation occurrence at LV pacing configurations		X	X	X		
	NYHA functional class	X			X		X
	QRS duration	X		X	X		X
	Standard echo measurements	X			X		X
	Electrical delay measurements			X	X		
	QRS optimization			X	X		
	12-lead ECG during QRS optimization			X	X		
	Echo measurements and AV optimization			X	X		
	Optimal programming of the device			X	X		

*MPP* multipoint pacing, *ICD* implantable cardioverter defibrillator, *RA* right atrium, *RV* right ventricle, *LV* left ventricle *NYHA* New York Heart Association, *ECG* electrocardiogram, *AV* atrioventricular

All the enrolled patients must be indicated for ICD implantation in accordance with the current guidelines. [3] (An ICD is recommended in order to reduce the risk of sudden death and all-cause mortality in patients with symptomatic HF (NYHA Class II–III) and an LVEF ≤ 35% despite ≥ 3 months of OMT, provided they are expected to survive substantially longer than 1 year with good functional status).

### Implantation procedure

The implantation procedure will be carried out within 30 days of enrollment. All subjects will receive either a market-approved St. Jude Medical (Saint Paul, MI, USA) CRT device that includes the MPP feature (models numbers CD3271-40(Q), CD3371-40(Q), CD3371-40C (QC) or newer) and a St. Jude Medical quadripolar left ventricular lead (Quartet 1458Q or newer) or a market-approved St. Jude Medical ICD device. Any commercially available and CE-marked right atrial and right ventricular leads may be implanted. A Merlin® Patient Care System (model 3650 or newer) programmer will be used to interrogate and program all devices on implantation and during follow-up. Post-implantation fluoroscopic images in two views will be required to document lead locations. Before hospital discharge, patients with an MPP device will undergo A-V delay optimization by means of the Ritter method, in order to maximize diastolic filling [20]. During this session, two MPP pacing vectors will be selected from the quadripolar lead. The pacing vectors will be selected to minimize interventricular conduction delay. Following selection of the two MPP vectors, V-V timing optimization will be performed according to the optimal pacing intervention identified by means of QRS duration criteria to avoid lengthening of the QRS duration. In the ICD group, every physician can decide to implant a ventricular (VVI) or traditional dual-chamber (DDD) ICD, but programming must be VVI 40 bpm [21, 22]. In case of LV lead implant failure the patient will be considered a dropout on treatment analysis.

### Study measurements and endpoints

All patients enrolled will undergo a baseline examination for collection of the following information: medical history and clinical evaluation, assessment of QRS duration, assessment of New York Heart Association (NYHA) functional class, echocardiographic examination, including evaluation of LV volumes and LVEF, mitral regurgitation grade, and inter- and intraventricular dyssynchrony estimation [23]. Plasma brain natriuretic peptide (BNP) levels will also be collected at the baseline and all follow-up visits. A complete echocardiographic analysis will be performed at the baseline and follow-up visits. The echo data will be analyzed by a central echo core laboratory, which will be blinded to allocation.

All data will be collected on an online database created for this study. Every effort will be made to ensure compliance with this schedule.

If a visit is missed for any reason, data on endpoints and adverse events will be collected at the subsequent visit.

All deaths will be reported immediately to the coordinator center.

### Primary endpoint

The primary endpoint is the percentage of patients who display reverse remodeling in the MPP group, in comparison with the ICD group, at the 12-month follow-up examination. Reverse remodeling is defined as a decrease in LVESV > 15% from the baseline [20].

### Secondary endpoints

The secondary endpoints are: the percentage of patients presenting with reverse remodeling in the MPP group compared with the Standard ICD group at the 24-month follow-up examination; the percentage of patients in each group who have an absolute increase of > 5 points in LVEF at the 12- and 24-month follow-up examinations; the percentage of patients with a BNP value < 400 pg/mL at the 12-month follow-up compared between groups.

Echocardiographic images will be acquired by the echocardiography laboratory at each participating center. Pavia Hospital (Fondazione IRCCS San Matteo, Pavia, Italy) will serve as the blind central core laboratory for the analysis of all echocardiographic results.

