## Methods

### Study population and randomization

This study is a prospective, randomized, multicenter, physician-initiated, pilot study. This is a parallel and superiority study. The study will be conducted at several Italian centers (up to nine high-volume Italian hospitals). Enrollment will begin in 2016 and is expected to continue through the beginning of 2017, until the predefined target number of patients has been reached. The expected duration of the investigation will be approximately 2–3 years, with 24 months of follow-up for each patient. Prior to enrollment, approximately 70–80 patients will be screened by means of an echo-dobutamine stress (DSE) test in order to evaluate the presence of left ventricular contractile reserve. Low-dose dobutamine stress echocardiography (LDSE) is a simple, cost-effective, and widely available method of identifying contractile reserve in the LV [18, 19]. The dose of intravenous dobutamine will be increased in 5 μg kg^−1^ min^−1^ increments every 5 minutes up to a recommended maximum dose of 20 μg kg^−1^ min^−1^. The test will be terminated in the event of arrhythmias or the occurrence of any complications or side effects. Measurements (offline) of end-diastolic and end-systolic volumes will be assessed at each infusion rate by two-dimensional echocardiography (biplane disk method). The left ventricular ejection fraction (LVEF), measured offline by means of Simpson’s biplane quantitative method, will be determined at each infusion rate (including baseline). An absolute increase of 5 points or higher in LVEF above the baseline will demonstrate the presence of LV contractile reserve and will be considered a positive LDSE test [18]. Only patients who have a positive LDSE test will be enrolled if they meet the inclusion criteria reported in Table 1.

**Table 1 Tab1:** Inclusion/exclusion criteria

A. Inclusion criteria
● HF with NYHA class II/III ● LVEF < 35% in patients on OPT for at least 3 months and candidate for ICD ● Patients with left ventricular contractile reserve at low-dose dobutamine stress echocardiography test
● QRS duration: 100–130 ms
● Ability and willingness to comply with study requirements
● Successful quadripolar LV lead implantation (only for treatment group)
B. Exclusion criteria
● Myocardial infarction, unstable angina within 40 days prior to enrollment
● Cardiac revascularization (PTCA, stent or CABG) in the 4 weeks prior to enrollment or planned for the 3 months following enrollment

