● Cerebrovascular accident (CVA) or transient ischemic attack (TIA) in the 3 months prior to enrollment
● Primary valvular disease
● Inability to comply with the follow-up schedule
● Age less than 18 years
● Pregnancy or intention to become pregnant during the period of the investigation
● Classification of status 1 for cardiac transplantation or consideration for transplantation over the next 12 months
● Previous cardiac transplantation
● Life expectancy < 12 months
● Permanent atrial fibrillation

*HF* heart failure, *NYHA* New York Heart Association, *LVEF* left ventricular ejection fraction, *OPT* optimized therapy, *ICD* implantable cardioverter defibrillator, *LV* left ventricle, *PTCA* percutaneous transluminal coronary angioplasty, *CABG* coronary artery bypass graft surgery

Patients who meet the eligibility criteria and do not have any exclusion will be recruited by the clinical cardiology groups associated with each enrolling center. Logs will be kept at each center of all identified patients who meet the clinical eligibility criteria. For eligible patients who are not enrolled, the reason for non-enrollment (exclusion) will be recorded.

The enrolled patients will be randomized in a 1:1 fashion to an MPP group or a Standard ICD group (control group).

Randomization will be centralized and stratified by center in order to obtain a balanced distribution of the devices implanted at each center. The random assignment to one of the two study groups will be made by the clinical research organization (CRO) and transmitted to the enrolling clinical center by logging on to a web-based automated program.

A flow diagram of patients in the study and a list of all investigational specific activities/procedures (Additional file 1) are shown in Fig. 1 and Table 2.

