### Sample size calculation

A main trial designed to show an effect size of +23% - from a proportion of success of 17% to an expected proportion of success of 40% - with alpha = 5% and power = 90% would require us to enroll 79 patients per group (total 158 patients). In the pilot study, recruiting, randomizing and analyzing 50 participants (25 per group), assuming that 17% approximately four patients) would respond in each group, would produce a 13% upper limit of the one-sided 90% confidence interval; this would exclude us finding a 23% difference, which would be statistically significant in a larger trial. In the event of 10% attrition (23 patients per group enrolled. i.e., incomplete data set due to deviation from protocol, implant failure or missing follow-up) the upper limit of the one-sided 90% confidence interval will be extended to 14.5%. If attrition is higher than 10%, a corresponding increase in sample size will be considered, in order to obtain 45–50 evaluable patients.

Finally, it has been estimated [18] that 30% of the screened patients will have a negative LDSE test. Therefore, about 70–80 patients will be screened for participation in the study, 70% of whom are likely to be enrolled and randomized in the study.

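### The BNP secondary endpoint is a 12-month status with no baseline reference, which costs precision and interpretability in a 50-patient pilot, and Table 2 has no BNP row

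*Protocol article*

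**What the plan says.** The Secondary endpoints section of the protocol article defines the BNP endpoint as "the percentage of patients with a BNP value < 400 pg/mL at the 12-month follow-up compared between groups". The definition mentions neither the baseline value nor a restriction to patients at or above 400 pg/mL at entry.

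The imaging endpoints are built differently. For the primary endpoint, "Reverse remodeling is defined as a decrease in LVESV > 15% from the baseline". A further secondary endpoint is "the percentage of patients in each group who have an absolute increase of > 5 points in LVEF". Both measure change within the patient.

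The inclusion criteria in Table 1 (for example "HF with NYHA class II/III") cover functional class, LVEF, contractile reserve and QRS duration. Neither they nor the exclusion criteria set a BNP level. On allocation, "Randomization will be centralized and stratified by center in order to obtain a balanced distribution of the devices implanted at each center"; BNP is not a stratification factor. The Sample size calculation section plans 25 patients per group.

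On collection, the section Study measurements and endpoints states that "Plasma brain natriuretic peptide (BNP) levels will also be collected at the baseline and all follow-up visits". Table 2 is captioned "List of all investigational-specific activities/procedures". It has rows for NYHA class, QRS duration and standard echo measurements, but none for BNP at any visit in either arm.

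**The concern.** A fixed cut at 12 months, with no entry level and no baseline term, mixes two kinds of success: patients whose BNP came down, and patients who were never above the cut. To take invented values, a patient who enters at 150 pg/mL and stays there is a success, while one who falls from 2000 to 450 is a failure. The percentage therefore says little about response unless the reader also knows who started where.

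With 25 per arm and stratification by center only, the two arms may well start with different proportions below 400, and part of that difference will remain at 12 months. Cutting a continuous marker and leaving out its baseline value also discards information that the trial already plans to collect. The pilot's results are meant to inform a larger trial, so a readable and reasonably precise BNP estimate is worth having.

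The schedule table is a separate and simpler matter. The text schedules BNP, and the table presented as the complete list of procedures omits it.

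**Working it through.** **No figure of the plan's own to reproduce.** The article gives no baseline BNP distribution, no expected percentage below 400 and no precision for this endpoint. From the document: n = 25 per arm, the 400 pg/mL cut, no entry level, stratification by center only. Assumed: proportion below 400 at baseline, p = 0.3–0.7; correlation r = 0.5–0.7 between baseline and 12-month log BNP; bivariate normal log BNP with the same distribution at both times.

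**1. Chance imbalance at baseline.** The SD of the between-arm difference is √(2p(1−p)/25).
- p = 0.3 or 0.7: √(2 × 0.21/25) = 0.130
- p = 0.5: √(2 × 0.25/25) = 0.141

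Exact probabilities from two independent binomials with n = 25:

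| Difference between arms | p = 0.3 or 0.7 | p = 0.5 |
|---|---|---|
| at least 3 patients (12 points) | 0.44 | 0.48 |
| at least 5 patients (20 points) | 0.16 | 0.20 |

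**2. How much carries to 12 months.** The carry-over coefficient is P(below 400 at 12 months, given below at baseline) minus P(below 400 at 12 months, given not below at baseline). For p = 0.5 the probability of being below at both times is 1/4 + arcsin(r)/(2π).
- r = 0.5: joint 0.333; 0.667 − 0.333 = 0.33
- r = 0.7: joint 0.373; 0.747 − 0.253 = 0.49
- p = 0.3 or 0.7 (bivariate normal integral): 0.32 at r = 0.5, 0.48 at r = 0.7

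The coefficient therefore runs from 0.32 to 0.49. A 12-point baseline difference shifts the expected 12-month difference by 12 × 0.32 ≈ 4 to 12 × 0.49 ≈ 6 points. A 20-point difference shifts it by about 6 to 10 points.

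**3. Information kept by the cut.** Relative to baseline-adjusted log BNP, for small effects, efficiency is φ(c)²/(p(1−p)) × (1−r²), where c is the normal quantile of p. The first factor is the loss from cutting; the second is the loss from not using baseline.
- p = 0.5: 0.399²/0.25 = 0.637
- p = 0.3 or 0.7: 0.348²/0.21 = 0.576

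| | r = 0.5 (× 0.75) | r = 0.6 (× 0.64) | r = 0.7 (× 0.51) |
|---|---|---|---|
| p = 0.5 | 0.48 | 0.41 | 0.32 |
| p = 0.3 or 0.7 | 0.43 | 0.37 | 0.29 |

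The range is 29–48%. Put differently, 25 patients per arm analysed by the cut give about what 25 × 0.29 ≈ 7 to 25 × 0.48 = 12 per arm would give with adjusted log BNP.

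**4. Who makes up the successes.** A wider set of assumptions was also tried: baseline median 200–800 pg/mL, log-SD 0.8–1.0, correlation 0.5–0.85, a 30% BNP reduction with MPP and no change with ICD. The share of 12-month successes already below 400 at baseline was:

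| Baseline median (pg/mL) | MPP arm | ICD arm |
|---|---|---|
| 200 | 81–88% | 83–93% |
| 400 | 61–73% | 67–82% |
| 600 | 46–64% | 53–76% |
| 800 | 36–58% | 43–72% |

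In this model the between-arm difference in the endpoint is about 10–17 points. The 4–6 point shift in step 2 can be read against that.

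**5. Text against table.** Study measurements and endpoints places BNP at baseline and all follow-up visits. Table 2 has an enrollment column and 6-, 12- and 24-month columns for each arm, and BNP appears in none of them. This needs no assumption.

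**The case against.** The strongest reply is that nothing here is biased. Allocation is randomised 1:1, so patients already below 400 are balanced in expectation. Chance imbalance is ordinary sampling error, and the confidence interval for a difference in proportions already covers it. A fixed threshold is a legitimate, if inefficient, pilot endpoint; the continuous values are collected, and an analysis plan that is not shown may adjust for baseline. The endpoint is secondary and affects neither the primary endpoint nor the sample size. All of this stands, and it limits the point to precision and interpretability. It does not remove the point: a baseline-adjusted analysis of the same binary outcome would still estimate a 12-month status rather than a response.

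Several stronger readings are tempting but unsupported:
- **That the endpoint mostly reflects who was already below 400.** This depends on a BNP distribution that the article does not give. Under the assumptions in step 4, the share falls to 36% in the MPP arm at a median of 800.
- **That a baseline imbalance passes straight into the result.** Only about a third to a half of it carries over.
- **That a BNP imbalance would feed the requirement that the intervention not be harmful.** The section on statistical analysis and decision-making does not name BNP as a measure of harm.
- **That baseline BNP goes unused.** The article does not say so.
- **That samples will be missed because Table 2 omits them.** The text schedules them plainly, the CRO and coordinator center monitor data completion by center, and Additional file 1, cited with the procedure list, is not shown. The gap is a mismatch to reconcile.

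**Conclusion.** The point holds as a loss of precision and interpretability on a secondary endpoint. That the endpoint lacks a baseline reference, that no BNP entry level exists, and that Table 2 omits BNP can all be read directly from the article. The result can be largely driven by baseline status; how far it is cannot be determined from the document.

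The sizes rest on the assumed 30–70% below 400 at baseline, the assumed correlation of 0.5–0.7 and a log-normal model. On those terms, a baseline difference of 12 points or more is close to an even chance, its expected effect at 12 months is modest, and more than half of the available information is given up throughout the range. The last of these is the main reason to change the endpoint.

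**What to change.** - **Endpoint.** Analyse log BNP at 12 months by ANCOVA with baseline log BNP as covariate, and report the between-arm ratio of geometric means with its confidence interval.
- **Descriptive count.** Keep the percentage below 400 pg/mL at 12 months, tabulated by arm and by baseline status (below 400, or 400 and above), so that patients who crossed the cut can be told from those who never exceeded it.
- **Table 2.** Add a BNP row at enrollment and at the 6-, 12- and 24-month visits in both arms, to agree with the section Study measurements and endpoints.

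The cost is a reworded endpoint and one table row; the text already plans the samples. The Trial status section reports four patients enrolled, so the change could be made early. The small downside is that the headline BNP result is no longer a simple percentage.

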### Protection of human subjects

At each clinical center, the routine follow-up interval history, physical examination, and device interrogation will be used to identify possible adverse events. Each physician is responsible for ensuring that the therapies rendered are consistent with the well-being of the patients.

If a situation arises where it is in the best interest of the patient that the programming be changed, the device will be programmed according to patient's need.

All information and data collected for the MPP Narrow QRS trial concerning subjects or their participation in this investigation will be considered confidential by all parties involved in the trial.

### Data monitoring and quality control

Study data will be monitored closely by the CRO and coordinator center (CC). Periodic reports will be generated on data completion and error rates for each clinical center.

In addition, all study data will undergo an extensive computer edit, and this information will be provided to the clinical centers to help improve and maintain data quality control procedures designed to detect inaccuracies and inconsistencies.

This information will be used to make decisions about relevant adjustment procedures in the study procedures.

All data are managed and maintained by the CC and the CRO.

### Rationale for the choice of a one-sided 90% confidence interval (CI)

For our pilot trial, we wish to identify a sample size that is large enough to meet the following requirements: (a) if the observed difference between the two groups in the pilot trial is zero, then the upper confidence limit will exclude the estimate that is considered “clinically significant” in the planned definitive trial; (b) reasonable confidence that our pilot trial is big enough to enable us to make the right decision on whether or not to proceed to a larger trial [24]. A 90% confidence interval would provide reasonable certainty regarding trial decision-making, but would be small enough to deliver a study within a reasonable budget and time frame. Furthermore, we propose to use a one-sided CI, as we are only interested in proceeding toward the main trial if there is some evidence of effectiveness. If the intervention appeared to be harmful, even if this effect were not statistically significant, we would not proceed.

### Sample size calculation

A main trial designed to show an effect size of +23% - from a proportion of success of 17% to an expected proportion of success of 40% - with alpha = 5% and power = 90% would require us to enroll 79 patients per group (total 158 patients). In the pilot study, recruiting, randomizing and analyzing 50 participants (25 per group), assuming that 17% approximately four patients) would respond in each group, would produce a 13% upper limit of the one-sided 90% confidence interval; this would exclude us finding a 23% difference, which would be statistically significant in a larger trial. In the event of 10% attrition (23 patients per group enrolled. i.e., incomplete data set due to deviation from protocol, implant failure or missing follow-up) the upper limit of the one-sided 90% confidence interval will be extended to 14.5%. If attrition is higher than 10%, a corresponding increase in sample size will be considered, in order to obtain 45–50 evaluable patients.

Finally, it has been estimated [18] that 30% of the screened patients will have a negative LDSE test. Therefore, about 70–80 patients will be screened for participation in the study, 70% of whom are likely to be enrolled and randomized in the study.

### Statistical analysis and decision-making process

The intervention effect will be reported as the difference in the proportions of success and 90% CI. No formal test of hypothesis will be undertaken, as we are only interested in whether the hypothesized treatment estimate is larger than 0. If in this pilot study with that sample size we find an estimate larger than zero, and the upper limit of the one-sided 90% confidence interval excludes the clinically relevant effect size of 23% under the null hypothesis, and the pilot also shows that it were feasible to recruit and retain the participants, and the intervention is not harmful, then the recommendation would be to move forward with the main study. Re-evaluation of the effect size to be used for sample size computation in the main study will take into account the results from the pilot study.

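### The go/no-go rule is inverted: the main trial may proceed only if the pilot rules out the 23-point effect that trial is meant to detect

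*Protocol article*

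**What the plan says.** The protocol article uses the upper confidence limit in three consecutive sections.

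- **Rationale for the choice of a one-sided 90% confidence interval.** The pilot should be large enough that "if the observed difference between the two groups in the pilot trial is zero, then the upper confidence limit will exclude the estimate" regarded as clinically significant for the definitive trial. The section adds that the team wants to go on only if there is some sign of effectiveness.
- **Sample size calculation.** The main trial targets an "effect size of +23% - from a proportion of success of 17% to an expected proportion of success of 40"%. In the pilot, about four responders in each group of 25 "would produce a 13% upper limit of the one-sided 90% confidence interval; this would exclude us finding a 23% difference". With 10% attrition (23 per group) the limit becomes 14.5%.
- **Statistical analysis and decision-making process.** The main study is recommended if the estimate is above zero, and "the upper limit of the one-sided 90% confidence interval excludes the clinically relevant effect size of 23% under the null hypothesis", and recruitment and retention prove feasible, and there is no harm. The same section says: "The intervention effect will be reported as the difference in the proportions of success and 90% CI".

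**The concern.** In the first two sections, a limit below 23 points means that the target effect has been ruled out. It is a futility bound. In the third section the same event is a condition for going ahead, joined by 'and' to a positive estimate. Read as written, the rule asks the pilot to show that the effect is probably too small, and then recommends a 158-patient trial powered to find that effect.

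The go/no-go recommendation is the decision this pilot is sized for. An inverted rule would favour the main trial when MPP does nothing and block it when MPP works as hoped. It would also leave the team to choose, with results in hand, between following the rule and overriding it.

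**Working it through.** **Inputs (Sample size calculation; Study population and randomization).** Control response 17%, MPP response 40%, difference 23 points; 1:1 allocation; 25 per arm, or 23 after attrition; one-sided 90% limit, z = 1.2816.

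**1. The plan's own figures.**

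- Main trial, pooled two-proportion formula, two-sided alpha 5%, power 90%, mean proportion 0.285: n = [1.960·√(2·0.285·0.715) + 1.2816·√(0.17·0.83 + 0.40·0.60)]² / 0.23² = 78.9, so 79 per group. This matches. The sidedness of alpha is not stated; one-sided would give 65.
- Pilot limit at zero difference, 4/25 in each arm: 1.2816·√(2·0.16·0.84/25) = 13.3%. This matches the stated 13%.
- With 23 per arm the same formula gives 14.2% (at 17%) to 14.3% (at 4/23), close to the stated 14.5%.

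The sample-size arithmetic is sound. These limits are drawn around a difference of zero.

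**2. The rule applied to possible results.** Upper limit = d + 1.2816·√[p₁(1−p₁)/n + p₀(1−p₀)/n], with 4/25 ICD responders:

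| MPP responders | Difference | Upper limit | Rule as written |
|---|---|---|---|
| 4/25 | 0% | 13.3% | no go (estimate not above 0) |
| 5/25 | 4% | 17.9% | go |
| 6/25 | 8% | 22.4% | go |
| 7/25 | 12% | 26.9% | no go |
| 10/25 | 24% | 39.7% | no go |

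For 10/25 the sum is 0.24 + 1.2816·√(0.40·0.60/25 + 0.16·0.84/25) = 0.24 + 0.157 = 0.397. At exactly 40% against 17% the limit is 38.8%. With 4/23 controls, only 5/23 passes (19.3%); 6/23 already fails (24.2%).

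**3. Probability of a go.** All pairs of responder counts were enumerated from two independent binomials, with control response 17%:

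| Rule | 25/arm, no effect | 25/arm, +23 points | 23/arm, no effect | 23/arm, +23 points |
|---|---|---|---|---|
| As written: estimate > 0 and limit < 23% | 24.8% | 5.4% | 23.0% | 5.6% |
| Estimate > 0 only | 42.5% | 95.5% | 42.1% | 94.7% |
| Reversed: estimate > 0 and limit ≥ 23% | 17.7% | 90.1% | 19.1% | 89.0% |

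A Newcombe limit at 25 per arm gives 23.8% and 5.4% as written, and 18.7% and 90.2% reversed, so the result does not depend on the Wald formula.

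**4. The other reading.** Suppose the null-hypothesis qualifier means an interval drawn around zero. Since p(1−p) is at most 0.25, that limit is at most 1.2816·√(0.5/n): 18.1% with 25 per arm and 18.9% with 23. It stays below 23% at any response rate once n exceeds 1.2816²·0.5/0.23² = 15.5 per arm. At the planned size the condition cannot fail, and only the positive estimate decides.

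**5. Which limit.** If the reported 90% interval is two-sided, its upper end is a one-sided 95% limit. Used in the rule as written, it gives 11.9% with no effect and 0.6% at +23 points.

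**The case against.** The strongest defence rests on the qualifier about the null hypothesis. Read with the rationale section, it may describe the design property that the limit is 13% at zero difference, and not a check on the observed interval. The stated interest in whether the estimate exceeds zero supports this. On that reading a result of 10/25 against 4/25 is a go, and the rule points the right way (42.5% with no effect, 95.5% at +23 points). The fault would then be leniency, not inversion.

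This reading is possible, but it does not rescue the rule. The condition is listed among things the pilot must find before a recommendation, and on this reading the planned data could never fail it. The interval on which the sample size is justified would play no part in the decision.

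Three smaller points stand:

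- The limit around zero also depends on the response rate, so 13% and 14.5% are not its only possible values. It could matter if evaluable numbers collapsed below about 16 per arm.
- The reported 90% interval may simply be shorthand for the one-sided interval proposed earlier, so that point is a clarification only.
- The reversed rule is stricter than a positive estimate alone. Against 4/25 controls, 5 or 6 MPP responders would become a no-go, and correct go falls from 95.5% to 90.1%. In return, false go falls from 42.5% to 17.7%.

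**Conclusion.** The concern holds. As written, the decision rule contradicts the rationale and sample-size sections. It is between four and five times as likely to recommend the main trial when MPP has no effect as when it has the planned effect (24.8% against 5.4%). That any observed benefit of 23 points or more fails needs no distributional assumption, because an upper limit cannot fall below its estimate. The probabilities assume a 17% control response, 25 evaluable patients per arm and a Wald limit; they change little with 23 per arm or a Newcombe limit. They cover the statistical conditions only, not the feasibility and harm conditions. The alternative reading leaves a rule in which the confidence limit does no work. Neither reading is usable, so the rule must be corrected.

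**What to change.** Amend the decision sentence to this effect: recommend the main trial if the estimated difference is above zero, the upper one-sided 90% limit of the observed difference is 23 points or more, recruitment and retention are feasible, and there is no sign of harm; do not proceed if that limit is below 23 points. Delete the reference to the null hypothesis. State that the deciding limit is the upper end of a two-sided 80% interval, and say whether the reported 90% interval is one- or two-sided. Quote the operating characteristics: about 18% false go and 90% correct go at 25 per arm with a 17% control response.

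At 23 to 25 per arm, a limit of 23 points or more already implies a positive estimate, because the limit is at most 18.9% when the estimate is zero or negative. The first condition can stay for clarity.

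If the sponsor prefers to decide on a positive estimate alone, the protocol should say so openly, drop the confidence-limit condition and state the 42.5% false-go rate.

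The cost is one sentence by amendment, with no extra patients or data. The article reports four patients enrolled at publication, so the change could be made before any 12-month comparison was available.
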